### Secondary outcome measures

The secondary outcomes include intervention tolerability (based on qualitative interviews and reported adverse events), retention (men successfully followed up at 6 months, as a proportion of those who were recruited to the trial and randomised into a study arm), change in PSA (a protein produced by cells of the prostate gland, which is often elevated in men with prostate cancer) [35] and insulin-like growth factor (IGF-I) levels (raised IGF-I levels are increasingly being implicated as a potential risk factor for cancer) [36] and change in all other data collected between intervention groups at the different time points. We will explore whether biomarkers of lycopene for the lycopene intervention arm, alpha-carotene, beta-carotene, lutein, lycopene, total carotenoids and vitamin C for fruit and vegetable intake, and phyto-oestrogen, as a biomarker for soya milk, are affected by the proposed interventions. Full details of the data being collected at specific time points are described in Table 2. The study was not powered for secondary outcomes.

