### Analysis plan

The primary comparative analyses will be by intention-to-treat. Baseline characteristics of each group will be tabulated using means and standard deviations for normally distributed data, medians and interquartile ranges for non-normally distributed data, and percentages and counts for categorical data. Randomisation rate and adherence to the intervention will both be reported as a percentage, along with the respective 95 % confidence interval.

We will also conduct exploratory analyses of change in physical activity and fruit and vegetable consumption (as measured for adherence to the interventions) will be analysed using a two-way ANOVAs or appropriate non-parametric tests if necessary. Change in selected secondary outcomes (IGF-I, PSA and blood biomarkers) will be analysed similarly, although this study is not powered for secondary outcomes. These analyses will focus on the main effects of the interventions, but we will also explore possible interactions between the interventions with respect to these outcomes. Assuming 80 men are recruited into the trial, this will provide approximately 90 % power to detect a large main effect size (f = 0.4) with an alpha level of 0.05, analysing the study as a 2 x 3 factorial design (power will be reduced after correcting for multiple testing). We will also explore associations between baseline Stage of Change; behavioural, normative and control beliefs; and adherence to the interventions using chi-square tests and logistic regression models.

Qualitative data collected during this research will be analysed thematically using a qualitative method, such as the framework approach [38]. Individuals will not be identified by name in the written transcript. A qualitative analysis computer programme, such as NVivo [39], will be used to assist analysis.

The SPIRIT 2013 checklist [40] and the CONSORT statement [41] were followed and adhered to during the development of the trial protocol and implementation. The PrEvENT trial has been given full ethical approval by Cornwall and Plymouth Research Ethics Committee (REC), ref: 14/SW/0056, and registered on the ISRCTN registry, ref number ISRCTN99048944. All participants provide fully informed consent.

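### Change in IGF-I, PSA and blood biomarkers is to be compared by ANOVA without adjusting for the trial-baseline value, which loses precision that data already collected could recover

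*Protocol article*

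**What the plan says.** The Analysis plan section of the protocol article first sets the method for change in physical activity and in fruit and vegetable intake, work that it labels exploratory: this "will be analysed using a two-way ANOVAs or appropriate non-parametric tests if necessary". It then carries that method over to the blood outcomes: "Change in selected secondary outcomes (IGF-I, PSA and blood biomarkers) will be analysed similarly". The section adds that the trial has no planned power for these outcomes. Main effects are the focus and interactions are explored.

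The same section gives a power statement that assumes 80 randomised men, a 5 % significance level and the six-cell factorial layout. It claims "approximately 90 % power to detect a large main effect size (f = 0.4".

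Table 2 lists blood samples at the cohort baseline (before surgery), at the true trial baseline (after surgery) and at 6 months, but not at 3 months. The section on recruitment into the randomised trial confirms blood sampling at the post-surgery consent appointment and at 6 months. The Analysis plan mentions no baseline covariate and does not say which of the two baselines change is measured from. The Secondary outcome measures section describes PSA as "a protein produced by cells of the prostate gland", and the Initial recruitment phase section says that the gland is taken out at surgery.

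**The concern.** A change score subtracts the whole baseline value, which amounts to fixing the regression slope on baseline at 1. When the true slope is smaller, the subtraction adds baseline noise to the outcome. A linear model with baseline as covariate estimates the slope and removes only as much as the data support. In large samples it is never less precise. The baseline bloods are already being collected, so the plan gives up this precision for nothing. The non-parametric fallback does not help, because it too would be applied to change.

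What is at stake is the width of the confidence intervals for the biomarker contrasts in a trial of about 80 men. PSA needs particular care. Its two candidate baselines lie on either side of removal of the organ that makes it, so the choice of reference could change the noise in the contrast a great deal.

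**Working it through.** **1. The plan's own power figure.** Inputs from the Analysis plan: N = 80, f = 0.4, alpha = 0.05, six cells. The noncentrality is N × f² = 80 × 0.16 = 12.8, with 80 − 6 = 74 denominator degrees of freedom. The noncentral F distribution gives 89.1 % for the three-level nutrition factor and 94.2 % for the two-level activity factor. The stated figure of about 90 % is reproduced for nutrition, and there is no error in it.

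**2. Variance of the two analyses.** Let r be the correlation between the baseline and 6-month values (not in the article, so assumed). Take equal standard deviations and set the 6-month variance to 1.

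- Change score: 2(1 − r)
- Baseline-adjusted: 1 − r²
- Ratio, change to adjusted: 2(1 − r)/(1 − r²) = 2/(1 + r)
- Men needed with adjustment to match 80 analysed by change: 80 × (1 + r)/2

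| r (assumed) | Change | Adjusted | Ratio | Interval width ratio (√) | Matching N |
|---|---|---|---|---|---|
| 0.3 | 1.40 | 0.91 | 1.54 | 1.24 | 52 |
| 0.5 | 1.00 | 0.75 | 1.33 | 1.15 | 60 |
| 0.7 | 0.60 | 0.51 | 1.18 | 1.08 | 68 |

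**3. What this does to power.** The article does not say which standard deviation f = 0.4 refers to, so both readings are shown for the nutrition factor. The adjusted model has 73 denominator degrees of freedom.

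- *f on the 6-month standard deviation.* Then f becomes 0.4/√(2(1 − r)) for change and 0.4/√(1 − r²) with adjustment. Power for change against adjustment is 76.0 % against 91.8 % at r = 0.3, 89.1 % against 96.1 % at r = 0.5, and 98.7 % against 99.5 % at r = 0.7.
- *f on the change-score standard deviation.* Change has 89.1 % throughout. Adjustment gives 98.0 %, 96.1 % and 93.6 % at r = 0.3, 0.5 and 0.7.

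Below r = 0.5, 2(1 − r) exceeds 1, so the change score is less precise than ignoring baseline altogether. At r = 0.2, on the first reading, power is 69.9 % for change, 89.1 % for the unadjusted 6-month value and 90.3 % with adjustment.

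**4. Unequal standard deviations.** Let k be the baseline standard deviation divided by the 6-month one. The change-score variance is 1 + k² − 2rk, and the adjusted variance is still 1 − r². The two are equal only when the slope r/k is 1. For example, at k = 0.5 and r = 0.5, 1 + 0.25 − 0.5 = 0.75 and 1 − 0.25 = 0.75.

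**5. PSA and the choice of reference.** Suppose, for illustration only, that the pre-surgery standard deviation is five times the 6-month one and r = 0.5. Change from the pre-surgery value then has variance 1 + 25 − 5 = 21, against 1 for the unadjusted 6-month value and 0.75 with adjustment (0.75/21 = 0.036). Such a change score would mostly reflect the pre-surgery value. The article gives no PSA figures, so this shows the direction of the effect and does not estimate its size.

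**The case against.** The strongest reply is that these analyses are labelled exploratory or explicitly unpowered, cover only selected secondary outcomes, and do not touch the co-primary outcomes, which are percentages with 95 % confidence intervals. That stands and limits the weight of the point. It is also fair that an article may leave the reference baseline to the full protocol or analysis plan, and that calling the post-surgery visit the true trial baseline suggests the answer. The unnamed reference is therefore a wording gap. The comparison of change by ANOVA, however, is stated outright and has not been left to another document.

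The size of the gain is uncertain too. It depends on r, shrinks as r rises (a ratio of 2/1.8 = 1.11 at r = 0.8), and vanishes when the slope on baseline is 1.

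A reader might infer more than the article supports:

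- *That change scores bias the comparison.* Both baselines precede randomisation, so the contrasts are unbiased over randomisation. Chance imbalance is already part of the variance counted above. Nor is the cell size of about 13 (80/6) the relevant number, because the main-effect comparisons are about 40 against 40 for activity and about 27 per nutrition arm.
- *That a PSA analysis from the pre-surgery value would show a surgery effect.* Every randomised man has had surgery, so its effect is common to all six cells and drops out of the contrasts between arms. Only noise is added.
- *That PSA change is uninformative.* This would need an assay floor and a proportion of men at it, and the article gives neither. A rise from the post-surgery value could still be seen. If there were a floor, it would limit the baseline-adjusted analysis as well.
- *That the same fix applies directly to activity and fruit and vegetable intake.* Those are analysed as measured for adherence. Table 2 lists the daily form only during the intervention, so that measure has no trial-baseline value to adjust for.

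**Conclusion.** The point holds as one of efficiency. For IGF-I, PSA and the blood biomarkers, the planned ANOVA of change gives a contrast with 1.54, 1.33 or 1.18 times the variance of the baseline-adjusted analysis at r = 0.3, 0.5 or 0.7. Confidence intervals are about 24 %, 15 % or 8 % wider. This rests on an assumed correlation and on equal standard deviations at the true trial baseline and 6 months. There would be no loss if the slope on baseline were 1. No bias over randomisation is shown, the plan's power figure is reproduced, and the feasibility conclusions on randomisation and adherence do not depend on it. For PSA, the supported conclusion is that the post-surgery sample should be the stated reference. The change is worth making because it uses data already collected, but the stakes are modest.

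**What to change.** For IGF-I, PSA and each blood biomarker, analyse the 6-month value in a linear model with the physical activity factor, the nutrition factor and the true-trial-baseline (post-surgery) value as covariate. Use the log scale for outcome and covariate where the marker is skewed, and add the interaction term for the exploratory interaction analysis. If the plan prefers to report change, the same covariate can be added to a model for change from that baseline. The arm estimates are then identical.

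State that change and adjustment both refer to the true trial baseline. For PSA, add the reason: the prostate is removed between the two baselines. Splitting PSA into detectable and undetectable at 6 months is not recommended here as a replacement. It discards information and could leave few events, and the article gives no figures on which to judge that trade-off.

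The cost is a change of wording in the analysis plan and one degree of freedom per model (73 instead of 74 with 80 men). No new data are needed. Activity and fruit and vegetable intake would need separate wording. The food frequency and activity questionnaires are collected at the true trial baseline and could serve as covariates, but they are different instruments from the daily form.

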**Methods/design:**

The trial is factorial, randomising men to both a physical activity (brisk walking or control) and nutritional (lycopene supplementation or increased fruit and vegetables with reduced dairy consumption or control) intervention. The trial has two phases: men are enrolled into a cohort study prior to radical prostatectomy, and then consented after radical prostatectomy into a randomised controlled trial. Data are collected at four time points (cohort baseline, true trial baseline and 3 and 6 months post-randomisation).

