### Initial recruitment phase

Men are recruited to the trial via a consecutive opportunistic sample; that is, men who are conveniently accessible to the research team in the urology outpatients clinic and who meet the inclusion criteria are invited to participate until the sample size is reached and then are introduced to the study by a member of the clinical care team at the appointment where a decision about treatment is made. The expected duration between the appointment where a decision about treatment is made and surgery is approximately 4 weeks. Men who indicate an interest in the trial are directed to the research nurse for further information and given an initial research appointment where informed consent into the cohort is obtained and key data collected. Data that are obtained include i) a baseline questionnaire, including collection of information about diet, physical activity levels, mood and prostate symptoms and ii) blood samples used to assess baseline levels of nutritional biomarkers and biomarkers of prostate cancer progression, such as PSA. Men who consent will allow prostate tissue samples to be obtained from the prostate that is removed at surgery. The tissue is stored for future analysis. Full details of data collected at each time point can be found in Table 2. Each man’s National Health Service (NHS) number is also recorded for anonymous data linkage to routine NHS electronic datasets, such as the Cancer Registries and the Office for National Statistics Vital Statistics dataset. Recruitment into the cohort study will continue until the specified sample size (n = 100) has been reached.

**Table 2 Tab2:** Data collected during PrEvENT

Participant assessment	Who					When							
	Usual care team	Consultant	Research nurse	Participant	Research team	Pre-screening	Cohort baseline appointment	Surgery	Cohort follow-up/true trial baseline appointment	6-month intervention duration	3-month follow-up appointment	6-month follow-up appointment	Evaluation interview
Eligibility screening	X	X	X			X							
Informed consent			X	X			X		X				
Demographic data				X			X		X		X	X	
Family medical history				X			X		X		X	X	
Anthropometric data weight, height, % body fat			X				X		X		X	X	
Blood sample			X				X		X			X	
Diet data FFQ [43]				X			X		X		X	X	
Physical activity data Recent Physical Activity Questionnaire [44]				X			X		X		X	X	
Urinary symptoms ICSmale-SF [45]				X			X		X		X	X	

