Psychological measures POMS-SF [46] and Benefit Finding Scale [47]				X			X		X		X	X	
Health beliefs data Adapted from [37] and [32]				X			X		X		X	X	
Quality of life measures FACT-P [48]				X			X		X		X	X	
General health data SF-12 [49]				X			X		X		X	X	
Cancer related fatigue FACIT-Fatigue [48]				X			X		X		X	X	
Lifestyle data Drinking and smoking				X			X		X		X	X	
Accelerometry data				X			X		X			X	
Prostate tissue		X						X					
Pedometer data				X						X			
Daily monitoring data Step count, record of fruit, vegetable, dairy and lycopene intake				X						X			
Qualitative evaluation data				X	X								X

At 5 weeks post-surgery, all men are posted a follow-up data collection questionnaire and invited to a second appointment with the research nurse.

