### Recruitment into the randomised control trial

Men invited to participate in the RCT will have agreed to be contacted about further related research during the initial cohort recruitment phase. Along with the post-surgery follow-up data collection questionnaire, these men receive an invitation to participate in the RCT. They are telephoned by the research nurse and screened for trial eligibility. Inclusion and exclusion criteria for the RCT can be seen in Table 1. Where eligible, a research appointment is arranged for the following week, where a consent form is completed along with collection of blood samples and provision of an accelerometer (to capture intensity of physical activity) to wear continuously for the following week. All men are also provided with a pedometer (to measure daily step count), to wear for the 6-month duration of the trial. The data items that are being collected are listed in Table 2.

The men are randomised into both the nutritional and physical activity intervention arms of the trial and provided with instructions specific to their intervention allocation. They receive texts, emails and post relating to the trial interventions, including recipe ideas and motivational messages, as applicable to their allocated intervention, to encourage continuation of their trial arm intervention throughout the 6-month trial period. These contacts take place at 1, 2, 5, 8, 13, 15 and 18 weeks post-randomisation. They include gratitude for ongoing support of the research and a reminder of the importance of the data collected. Men are reminded of the changes they have been asked to make and the data they have been requested to record daily. Instructions are given of how to carry out the behaviour change, as well as being reminded of the potential benefits of the new behaviour, and men are informed that others similar to them carry out the intended behaviour. Message content was developed in line with the Theory of Planned Behaviour [32] (See Theoretical Underpinning below).

At 3 and 6 months following randomisation, the men attend a follow-up research appointment, where repeat questionnaires are completed. At the 6-month follow-up appointment, a blood sample is taken. For the final week of the trial, men wear an accelerometer to record the intensity of their physical activity.

We intend to recruit 100 men to the cohort, and of these, randomise at least 80 to the randomised controlled trial.

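### Arms are compared on change by two-way ANOVA, so one of two planned pre-randomisation measurements has no role; ANCOVA on both is a nearly free gain of uncertain size.

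*Protocol article*

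**What the plan says.** The Abstract (Methods/design) sets out the schedule: "Data are collected at four time points (cohort baseline, true trial baseline and 3 and 6 months post-randomisation". Randomised men come from the cohort: "Men invited to participate in the RCT will have agreed to be contacted about further related research during the initial cohort recruitment phase". Before surgery the cohort visit collects "a baseline questionnaire, including collection of information about diet, physical activity levels, mood and prostate symptoms" and "blood samples used to assess baseline levels of nutritional biomarkers and biomarkers of prostate cancer progression, such as PSA". The next reading comes after the operation: "At 5 weeks post-surgery, all men are posted a follow-up data collection questionnaire and invited to a second appointment with the research nurse". Eligible men then attend a trial appointment in the week after the screening call, which puts the trial baseline at about 5 to 6 weeks after surgery.

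Table 2 ticks the blood sample, food frequency questionnaire, activity questionnaire, urinary symptoms, mood, FACT-P, SF-12, fatigue scale and accelerometry at both the cohort baseline and the true trial baseline. It ticks the daily monitoring form for the intervention period only.

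The Analysis plan section names two-way ANOVA, or a non-parametric test if needed, for change in activity and in fruit and vegetable intake as recorded for adherence. For the blood outcomes, "Change in selected secondary outcomes (IGF-I, PSA and blood biomarkers) will be analysed similarly". It names no covariate and does not say from which baseline change is taken. It calls the activity and diet analyses exploratory and says that the study is not powered for secondary outcomes.

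**The concern.** Two readings of the same quantity before randomisation carry more information about a man's later level than one. A change score subtracts one of them with a fixed weight of 1 and ignores the other. With at least 80 men across six cells, residual variance limits what the secondary comparisons can show. The Analysis plan claims about 90% power only for a large effect (f = 0.4), and says that this falls after correction for multiple testing. The gap concerns the method that the article fixes, and not merely a detail left open: as stated, that method has no place for the second reading. At stake is precision only. Neither the change-score analysis nor the proposed one is biased by design.

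**Working it through.** **Step 1: the plan's own figure.** Inputs from the Analysis plan: N = 80, f = 0.4, alpha 0.05, 2 x 3 factorial. Noncentrality = f² x N = 0.16 x 80 = 12.8; error df = 80 − 6 = 74. The noncentral F distribution gives 89.1% power for the three-level nutrition factor (2 df) and 94.2% for the two-level activity factor (1 df). The stated figure of about 90% is reproduced for the nutrition factor.

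**Step 2: residual variance under three analyses.** Let r1 be the correlation of the trial baseline with follow-up, r0 that of the pre-surgery value with follow-up, and r01 that between the two baselines. None is in the document; all are assumptions. Variances are relative to the follow-up variance, taken as equal across visits, and change is taken from the trial baseline.

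- Change score: 2(1 − r1)
- ANCOVA on the trial baseline: 1 − r1²
- ANCOVA on both: 1 − (r1² + r0² − 2·r1·r0·r01)/(1 − r01²)
- Further fractional cut from the second reading: (r0 − r1·r01)² / [(1 − r01²)(1 − r1²)]

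| r1, r0, r01 | Change | One baseline | Both | Further cut |
|---|---|---|---|---|
| 0.7, 0.5, 0.7 | 0.60 | 0.51 | 0.510 | 0.04% |
| 0.5, 0.5, 0.5 | 1.00 | 0.75 | 0.667 | 11% |
| 0.7, 0.7, 0.7 | 0.60 | 0.51 | 0.424 | 17% |
| 0.5, 0.6, 0.5 | 1.00 | 0.75 | 0.587 | 22% |
| 0.4, 0.6, 0.4 | 1.20 | 0.84 | 0.610 | 27% |
| 0.4, 0.7, 0.4 | 1.20 | 0.84 | 0.493 | 41% |

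The first and last rows are the extremes of the assumed ranges (r1 0.4 to 0.7, r0 0.5 to 0.7, r01 0.4 to 0.7):

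- Low end: (0.5 − 0.49)² / (0.51 x 0.51) = 0.0001/0.2601 = 0.04%.
- High end: (0.7 − 0.16)² / (0.84 x 0.84) = 0.2916/0.7056 = 41%.

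**Step 3: where the gain comes from.** With all correlations 0.5, replacing change by one-baseline ANCOVA takes the variance from 1.00 to 0.75. The second reading then takes it to 0.667. So 0.25 of the total fall of 0.333 comes from dropping the change score, and 0.083 from the pre-surgery value.

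**Step 4: power in that case.** Take a moderate effect, f = 0.25 on the change-score scale, with N = 80 and one error df lost per covariate.

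| Analysis | Activity (1 df) | Nutrition (2 df) |
|---|---|---|
| Change score | 60% | 49% |
| ANCOVA, trial baseline | 72% | 61% |
| ANCOVA, both baselines | 77% | 67% |

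**The case against.** The strongest reply is that this is a condensed article, that covariates for exploratory models belong in an analysis plan not shown here, and that nothing stated is false. This stands in part: an unseen plan may already add covariates, so the point applies to the stated method only. But the article does not leave the method open. It names change and two-way ANOVA, and that combination excludes the second reading.

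Three stronger readings are tempting and are not supported.

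- A reader might infer that the trial baseline, taken during surgical recovery, is a weaker guide to the 6-month level than a habitual pre-surgery value. No section says so. The cohort visit itself follows the treatment decision, and Theoretical underpinning hypothesises that diagnosis prompts change in diet and activity, so the pre-surgery value is not clearly habitual. The rows of the table where r0 exceeds r1 depend on this unproven premise.
- A reader might infer that the pre-surgery data are discarded altogether. The same section implies a use for them in exploring natural change around diagnosis and treatment. What they lack is a stated role in the arm comparison.
- A reader might expect a worthwhile gain for every outcome. The gain can be nil. PSA is produced by the prostate, which is removed between the two readings, so its pre-surgery value is not a second reading of the same quantity. Urinary symptoms call for similar caution. Activity and fruit and vegetable intake are analysed from self-report during the intervention, an instrument with no pre-surgery value.

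It also stands that the decision thresholds of this feasibility trial (65% randomisation, 75% adherence) do not depend on any of this.

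**Conclusion.** The point holds as an optional gain in efficiency, not as an error that endangers the trial. For IGF-I, nutritional biomarkers, questionnaire scales and accelerometry, the schedule provides two pre-randomisation readings, and the stated analysis uses one at most. Beyond one-baseline ANCOVA, the second reading cuts residual variance by 0 to about 41% over the assumed correlation ranges, and by 11% when all three are 0.5, which is equivalent to 80 x 0.75/0.667 = 90 men instead of 80. The larger part of the gain in that central case comes from moving off the change score. The sizes rest on assumed correlations, equal variances across visits, and complete cohort-baseline data; the last is true by design but may not hold in practice. For IGF-I it is also assumed that the assay is run on the cohort blood sample, which Table 2 schedules but the recruitment text does not itemise.

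**What to change.** In the Analysis plan section:

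- For IGF-I, nutritional biomarkers, questionnaire scales and accelerometry, analyse the follow-up value in the 2 x 3 factorial model by ANCOVA, with the true trial baseline and the cohort-baseline value as covariates. Name the true trial baseline as the reference for any change that is reported.
- Leave the pre-surgery value out of the PSA model, and decide explicitly whether to use it for urinary symptoms.
- For activity and fruit and vegetable intake from the daily forms, allow the pre-surgery food frequency, activity questionnaire or accelerometry values only as proxy covariates, and label them so.
- State how missing cohort-baseline values are handled, so that no randomised man is dropped for lack of one.
- Confirm that the trial-baseline accelerometer week ends before allocation is known. The article has men wear the device in the week after the appointment and does not say when randomisation falls relative to it.

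The cost is a few sentences and one error degree of freedom per covariate (74 to 72 with both). No new data collection is needed.
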